#### Adolescent Psychotic-Like Symptom Screener

The Adolescent Psychotic-Like Symptom Screener (APSS) [59] is a seven-item measure designed to identify people who are at increased risk of future clinical psychotic disorder. In this study, only three items will be administered to assess paranoia, auditory and visual hallucinations. For each question, there are three possible responses: ‘Yes, definitely’, ‘Maybe’ and ‘No, never’. Responses are scored 1, 0.5 and 0 respectively. Higher total scale scores on this measure are indicative of greater psychotic-like symptoms. In the general population, this instrument has demonstrated good sensitivity and specificity in identifying young adolescents with psychotic-like experiences [59].

#### Pittsburgh Sleep Quality Index

The Pittsburgh Sleep Quality Index (PSQI) [60] was designed to assess sleep quality and disturbances over a 1-month interval. The PSQI consists of 19 items, which are used to compute seven component scores: sleep quality, sleep latency, sleep duration, habitual sleep efficiency, sleep disturbances, use of sleep medications and daytime dysfunction. Each item is weighted equally on a scale that ranges from 0 (no difficulty) to 3 (severe difficulty) scale. The seven component scores are then summed to yield a global score, ranging from 0 to 21; higher scores indicate worse sleep quality. The PSQI has demonstrated acceptable to good internal homogeneity, test–retest reliability and convergent validity across studies [60–62].

#### Child Health Utility 9D

The Child Health Utility 9D (CHU-9D) [63] is a nine-dimension generic preference-based measure designed to assess child and adolescent health-related quality of life and suitable for application in economic evaluation. Current child/adolescent health-related quality of life is assessed across the domains of worry, sadness, pain, tiredness, annoyance, school, sleep, daily routine and activities. Each dimension is rated on a 5-point response scale ranging from ‘no’ to ‘severe impairment’. Responses are then converted to utilities on the 0–1 dead to full health quality-adjusted life years (QALY) scale using a preference-weighted scoring algorithm [64]. Previous validation studies with adolescents from the community and mental health services have demonstrated that the self-complete instrument has acceptable internal consistency and convergent validity for children and adolescents aged 7–17 years [65–67].

#### Short Warwick–Edinburgh Mental Well-Being Scale

The Short Warwick–Edinburgh Mental Well-Being Scale (SWEMWBS) [68] is a shortened seven-item version of the 14-item Warwick–Edinburgh Mental Well-Being Scale (WEMWBS), which was developed to assess mental well-being in the general population. The SWEMWBS consists of seven statements about thoughts and feelings over the past 2 weeks. Ratings are made on a 5-point Likert scale (1 = ‘None of the time’, 2 = ‘Rarely’, 3 = ‘Some of the time’, 4 = ‘Often’, 5 = ‘All of the time’). Total scale scores are calculated by summing item scores and transforming the total score using a conversion table. Total scores can range from 7 to 35. A higher score indicates a higher level of mental well-being. The SWEMWBS has demonstrated adequate reliability and validity across studies [69, 70].

#### Demographic information

At the baseline assessment, participants will be asked to provide their date of birth, postcode, country of birth, language spoken at home, who they live with at home, Aboriginal and Torres Strait Islander status, and socio-economic status [71].

#### Height and weight

Self-reported height (cm) and weight (kg) will be provided.

#### Big Five Personality Inventory

The Big Five Personality Inventory (BFI-10) [72] is a 10-item scale measuring the Big Five personality traits: Extraversion, Agreeableness, Conscientiousness, Neuroticism and Openness. The scale was developed based on the 44-item Big Five Inventory (BFI-44) [73]. Respondents indicate their level of agreement with each described trait on a 5-point scale, ranging from 1 = ‘Disagree strongly’ to 5 = ‘Agree strongly’. Total subscale scores are calculated by summing item scores (two items per subscale). Subscale scores can range from 2 to 10. The BFI-10 has demonstrated acceptable test–retest reliability and good construct validity across studies [72, 74].

#### School connectedness

School connectedness will be assessed using questionnaire items developed by the Organisation for Economic Co-operation and Development (OECD) Programme for International Student Assessment [75]. Six items will be administered, which are rated on a 4-point scale from 1 (‘Strongly agree’) through to 4 (‘Strongly disagree’). Total scale scores can range from 6 to 24, with higher scores reflecting greater school connectedness.

#### Schuster Social Support Scale

The Schuster Social Support Scale (SSSS) [76] is a 15-item measure of positive and negative interactions with family, friends and spouse. In the current study, 10 items will be administered to assess interactions with family and friends only. Each item is rated on a 4-point scale ranging from 0 (‘Never’) through to 3 (‘Often’). Scores are interpreted per category, for friends and family, with higher scores on the supportive interactions scales indicative of more supportive interactions, and higher scores on the negative interactions scales indicate more negative interactions.

#### Maladaptive Facebook Usage Scale (adapted)

The Maladaptive Facebook Usage Scale [77] is a seven-item measure of maladaptive Facebook usage, which assesses an individual’s tendency to undertake negative social evaluations and social comparisons when they use Facebook. This scale has demonstrated good test–retest reliability and convergent validity [77]. In this trial, the scale has been adapted to incorporate social media more broadly. A screening item has been added asking respondents to nominate which social media platforms they use at least once per week. Options include: Facebook, Instagram, Snapchat, Tumblr, Twitter, YouTube, Reddit, Other and ‘I don’t use social media’. The seven items of the Maladaptive Facebook Usage Scale were adapted to apply to any social media platform (e.g. ‘I tend to read the social media status updates of others to see if they are feeling the way I am’ and ‘Reading the social media status updates of others tends to make me feel down on myself’). Items are rated on a response scale from 1 (‘Strongly disagree’) to 7 (‘Strongly agree’). Total scale scores can range from 7 to 49. Higher scores indicate greater tendencies to seek online social comparisons and negative evaluations.

#### Gender identification and sexual identification/preferences

Gender identification (two items: sex at birth and current gender identity) and sexual identification and preferences (one item for each) will be examined at baseline and annually between 12-month and 60-month follow-up.

#### Romantic relationships

Two items will be presented at multiple time points to assess romantic relationships. These items will ascertain the number of special or important romantic relationships in the past year, as well as the number of break-ups in the past 12 months.

#### Sexual behaviour

A series of questions will be presented at the 24-month follow-up when participants are in Year 10 (aged 15–16 years) to assess sexual behaviour, taken from the National Survey of Australian Secondary Students and Sexual Health [78]. These items will assess experience and age of first ‘making out’, intimate genital touching and sex, as well as number of people they have had sex with during the past year and frequency of condom use. This section will include an initial gating item assessing history of intimate sexual contact. Those who do not endorse this item will not receive the other sexual behaviour items.

#### Trauma Behavioural Risk Factor Surveillance System—Adverse Childhood Experience Module

The Trauma Behavioural Risk Factor Surveillance System—Adverse Childhood Experience Module (BRFSS-ACE) [79] consists of 11 items that assess exposure to nine types of adverse childhood experiences in the first 18 years of life, including: verbal abuse, physical abuse, sexual abuse, household mental illness, household alcohol abuse, household drug abuse, domestic violence, parental separation/divorce and incarcerated family members. The responses are dichotomised to indicate exposure and summed to create an ACE score ranging from 1 to 8 for each subdomain, with higher scores indicating greater exposure. Previous studies have demonstrated that this instrument has adequate internal consistency and validity [80, 81]. In this trial, the complete BRFSS-ACE will be administered at 48-month follow-up when participants are near 18 years of age. A modified version of the questionnaire consisting of eight items will be administered at baseline when participants are approximately 13 years old. This modified scale excludes items on physical and sexual abuse, and includes additional items assessing out-of-home or foster care and feelings of endangerment or physical harm.

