#### Suicidal Ideation Attributes Scale

The Suicidal Ideation Attributes Scale (SIDAS) is a recently developed brief measure of suicidal ideation severity in the past month. Using a general population sample, it has demonstrated high internal consistency and good convergent validity [49]. The SIDAS consists of five questions pertaining to frequency of thoughts, controllability of thoughts, closeness to attempt, level of distress associated with the thoughts and impact on daily functioning. Each item is assessed on a 10-point scale. Endorsement of item 3 (‘How close the individual has come to making an attempt in the last month’) will trigger the trial’s risk management procedure (see details later). A total scale score is calculated by summing item scores and can range from 0 to 50. Higher scores indicate higher levels of suicidal ideation severity.

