### Participant risk management protocol

An independent Data and Safety Monitoring Committee (DSMC) has been established to monitor the quality of trial data and the safety of research participants. The DSMC will be responsible for safeguarding the interests of participants through regular monitoring, including participant safety and adverse events. This group will be responsible for monitoring the efficacy of the interventions being tested on primary outcomes, as well as the overall conduct of the study, including recruitment, protocol compliance, accuracy and completeness of data collection. This group will also provide recommendations with respect to continuing, modifying or terminating the trial, on the basis of feasibility or safety concerns, and will have access to unblinded data. This group can recommend the trial team be unblinded if there are serious safety concerns and meets every 6 months to review trial conduct. There is no anticipated harm from this trial, as it involves a population-based sample and evidence-based interventions. However, should there be any unanticipated harms, this will be monitored by the DSMC, who will provide recommendations about care for affected participants.

All students involved in the trial will be assessed for suicidal thinking and behaviour at each assessment point, using the SIDAS and the YRBS. If participants indicate serious suicidal thinking, plans or behaviour on study surveys, an alert will be triggered whereby the research team and school counsellor are notified immediately using a purpose-built study portal. School counsellors will then follow-up with students within 48 h to offer immediate support, or refer on when necessary, which is recorded in the portal. The research team will monitor this portal and directly contact any counsellors who have not indicated follow-up with students. If students have changed or left schools, parents will be notified. At the 48-month assessment point, when students are in their final year of school, they will also be asked about history of sexual abuse. If students indicate an experience of sexual abuse, this same process of notifying the school counsellor will be followed, and schools will assume the duty of care for mandatory reporting requirements. This information will be communicated to relevant university and school ethics committees, as well as the DSMC following each assessment point.

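### The 48-month counsellor alert names sexual abuse but not physical abuse, which the same questionnaire asks about at the same visit

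*Protocol article*

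**What the plan says.** The Participant risk management protocol section of the protocol article describes one alert route. It starts with suicidality: "If participants indicate serious suicidal thinking, plans or behaviour on study surveys, an alert will be triggered". The research team and the school counsellor are told at once through a study portal. "School counsellors will then follow-up with students within 48 h to offer immediate support", or refer the student on, and the research team contacts any counsellor who has not recorded follow-up.

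The section then adds one trigger at the 48-month visit: "If students indicate an experience of sexual abuse, this same process of notifying the school counsellor will be followed". Responsibility for any report to the authorities is placed outside the research team, in the words "schools will assume the duty of care for mandatory reporting requirements".

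The section on the trauma measure (BRFSS-ACE) says what students are asked. At the later visit, "the complete BRFSS-ACE will be administered at 48-month follow-up when participants are near 18 years of age". The exposures it covers start with "verbal abuse, physical abuse, sexual abuse, household mental illness". At baseline, when students are about 13, a modified eight-item version leaves out physical and sexual abuse but "includes additional items assessing out-of-home or foster care and feelings of endangerment or physical harm". In Table 1 the trauma measure is scheduled at baseline and 48 months only.

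**The concern.** At 48 months a student may disclose physical abuse, sexual abuse or both on one questionnaire in one sitting. If the alert rule is followed as the article words it, a report of sexual abuse reaches the counsellor and the school takes up its reporting duties. A report of physical abuse alone sets nothing in motion. The article gives no reason for separating the two.

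What is at stake is the care of a young person who has told the study about physical abuse. The primary comparison, the error rate and the sample size do not depend on it.

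**Working it through.** No arithmetic applies. The check sets each sensitive item against the response that the article states for it.

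| Item | When asked | Response stated in the article |
|---|---|---|
| Serious suicidal thinking, plans or behaviour (SIDAS, YRBS) | Baseline and later assessments | Portal alert, counsellor follow-up within 48 h |
| Sexual abuse (complete BRFSS-ACE) | 48 months | Same alert; schools take on mandatory reporting |
| Physical abuse (complete BRFSS-ACE) | 48 months | None |
| Feelings of endangerment or physical harm (modified BRFSS-ACE) | Baseline | None |

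1. *Is the third row filled elsewhere?* The Setting section says that assessments fall within the school year so that risk issues can be dealt with promptly, but it names no item and no action. The Data and Safety Monitoring Committee monitors safety and unanticipated harms, and meets every six months. Neither is a response to an individual student's disclosure.

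2. *Could the school find out without an alert?* Students answer through a secure online portal, and under Data collection and management the answers are stored by ID code, apart from identifying details. The portal alert is the only route the article describes by which a counsellor would learn of an answer.

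3. *Who falls outside the rule?* A student who reports physical abuse and also triggers the suicidality or sexual-abuse alert is followed up anyway. The gap concerns students who report physical abuse and trigger neither.

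4. *Why physical abuse, and not every item on the instrument?* The article itself pairs physical with sexual abuse as the content withheld from the modified baseline scale and asked in full only near age 18. Having treated the two alike when deciding what to ask, it attaches a response to one of them. Of the two, 1 has a stated response.

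5. *Is there time to change it?* Under Trial design the waves were planned to start in July 2019, April 2020 and July 2020. Adding 48 months puts the full questionnaire at about July 2023, April 2024 and July 2024, well after the baseline visits.

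6. *The baseline items.* The article gives only a summary phrase. It does not show whether the questions concern current danger, a past event or a general feeling, so the right response cannot be worked out from the text.

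**The case against.** The strongest objection is that this is a journal article condensed from a full protocol, which the Ethics and dissemination section says is available on request. Item-level alert rules often sit in that document or in a separate risk procedure. Ethics approval from the university and approval through the state education process are also reported. Silence in the article is therefore weak evidence about what happens in the trial.

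Part of this stands, and it lowers confidence. It does not remove the point, because the article did not leave safeguarding to another document. It sets out the route, the time limit and the triggers, and the SIDAS section refers the reader forward to this procedure. A trigger list that takes one abuse type from an instrument asking about two is incompletely worded.

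Two stronger readings are tempting. A reader might infer that the trial has no response to physical abuse, or has decided against one. The documents do not support that: the article never calls sexual abuse the only abuse trigger, and the full protocol is not shown. A reader might also infer that the baseline endangerment items need the same automatic alert. That goes too far while their wording and time frame are unknown, and automatic disclosure of a 13-year-old's answers to the school is open to debate.

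**Conclusion.** The point holds for physical abuse at 48 months: the article states a counsellor alert for sexual abuse and no response to physical abuse reported on the same instrument at the same visit. For the baseline items it holds only as a question to the sponsor.

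Its size is one of two paired abuse disclosures without a stated follow-up. The document gives no endorsement rate, so no number of affected students is claimed. The conclusion assumes that the article's trigger list is the rule as operated; if the full protocol already covers physical abuse, only the article's wording is incomplete. It should be corrected, with medium confidence given that the full document was not available.

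**What to change.** In the Participant risk management protocol section, name reported physical abuse at 48 months beside sexual abuse, with the same portal alert and the same counsellor follow-up within 48 h. Leave decisions on mandatory reporting to the schools. If the full protocol already provides this, one sentence saying so is enough.

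For the baseline items on endangerment or physical harm, ask the sponsor to confirm what response applies to a positive answer. No automatic alert is prescribed.

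The cost is a short text change, a setting in the existing portal and some additional counsellor alerts at 48 months. The change is a protocol amendment, so under Ethics and dissemination it needs approval by the relevant ethics committees and listing on the registry. The information given to students and parents, which is not shown here, may need a matching line.

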#### History of mental health diagnosis

One item will assess the lifetime history of diagnosed mental health problems (major depression, social anxiety disorder, generalised anxiety disorder, obsessive compulsive disorder, panic disorder, alcohol use disorder, substance use disorder, attention deficit hyperactivity disorder, post-traumatic stress disorder, schizophrenia/psychosis).

#### Hospitalisation

One item will assess hospitalisation in the previous 12 months and will ask participants to distinguish between hospitalisation for physical and mental health problems.

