### Aims

This trial will investigate the impact of two mental health apps on adolescent depression. The first objective of this trial is to determine whether delivering a CBT programme via smartphone application can prevent high school students in Year 8 from developing depressive symptoms compared to students in the control arm. This study will assess the effect of the programme on a range of secondary outcomes, which include mental health symptoms (distress, anxiety, insomnia) at post intervention, 6, 12, 24, 36, 48 and 60 months. The effect of a second intervention on depression in those who show elevated depressive symptoms 1 year after using the first SPARX app will also be evaluated. Individual differences associated with response to the interventions will also be investigated, including demographics, history of mental illness, personality factors, social support, social media use and gender identification, among a range of other variables (see Table 1). In the control group, these factors will be examined as possible predictors for the development of depressive symptoms and other mental health problems.

**Table 1 Tab1:** Summary of primary, secondary and tertiary outcome measures, potential mediating and risk factors, and data collection time points

Outcome measure		Baseline	Post (Stage I)	6 months	12months	Post (Stage II)^a^	24 months	36 months	48 months	60 months
Primary outcome measure										
Depression	Patient Health Questionnaire: Adolescent Version (PHQ-A)	✓	✓	✓	✓	✓	✓	✓	✓	✓
Secondary outcome measures										
Psychological distress	Distress Questionnaire 5 (DQ5)	✓	✓	–	✓	–	✓	✓	✓	✓
Anxiety	Spence Children’s Anxiety Scale (SCAS) including Generalized Anxiety and Social Phobia subscales	✓	✓	–	✓	✓	✓	✓	✓	✓
Insomnia	Insomnia Severity Index (ISI)	✓	✓	–	✓	✓	✓	✓	✓	✓
Tertiary outcome measures, potential mediating variable risk factors										
Suicidal ideation	Suicidal Ideation Attributes Scale (SIDAS)	✓	✓	–	✓	–	✓	✓	✓	✓
Suicide behaviour	Youth Risk Behaviour Survey (YRBS)	✓	✓	–	✓	–	✓	✓	✓	✓
Externalising behaviours	Strength and Difficulties Questionnaire (SDQ)	✓	✓	–	✓	–	✓	✓	✓	✓
Eating disorders	Screen for Disordered Eating (SDE)	✓	✓	–	✓	–	✓	✓	✓	✓
Self-harm	Single question from Self-Harm Questionnaire	✓	✓	–	✓	–	✓	✓	✓	✓
Alcohol use	Questions from previous National Drug and Alcohol Research Centre, UNSW studies	✓	✓	–	✓	–	✓	✓	✓	✓

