Other substance use	Questions from Australian Institute of Health and Welfare 2007 National Drug Strategy Household Survey	✓	✓	–	✓	–	✓	✓	✓	✓
Psychosis	Adolescent Psychotic-like Symptom Screener (APSS)	✓	✓	–	✓	–	✓	✓	✓	✓
Sleep quality	Pittsburgh Sleep Quality Index (PSQI)	✓	✓	–	✓	✓	✓	✓	✓	✓
Quality of life	Child Health Utility 9D (CHU-9D)	✓	✓	–	✓	–	✓	✓	✓	✓
Well-being	Short-form Warwick–Edinburgh Mental Well-Being Scale (SWEMWBS)	✓	✓	–	✓	–	✓	✓	✓	✓
Demographics	Age, ethnicity, location, language, perceived socio-economic status	✓	–	–	–	–	–	–	–	–
Height and weight	Height (cm), weight (kg)	✓	–	–	✓	–	✓	✓	✓	✓
Personality	Big Five Inventory-10 (BFI-10)	✓	–	–	–	–	–	–	–	–
School connectedness	Items from OECD Programme for International Student Assessment (PISA)	✓	✓	–	✓	–	✓	✓	✓	–
Social support	Schuster Social Support Scale (SSSS)	✓	✓	–	✓	–	✓	✓	✓	✓
Social media use	Maladaptive Facebook Use Survey (MFUS), adapted to apply to social media use more broadly	✓	✓	–	✓	–	✓	✓	✓	✓
Gender identification	Sex at birth and current gender identification	✓	–	–	✓	–	✓	✓	✓	✓
Sexual identification and preferences	Single item for each	✓	–	–	✓	–	✓	✓	✓	✓
Sexual behaviour	History of sexual behaviour	–	–	–	–	–	✓		✓	
Romantic relationships	History of romantic relationships	✓			✓		✓	✓	✓	✓
Trauma	Adapted Behavioural Risk Factor Surveillance System—Adverse Childhood Experience (BRFSS-ACE)	✓ no abuse items	–	–	–	–	–	–	✓	–
History of diagnosed mental health condition	Diagnosed mental health conditions	✓	✓	–	✓	–	–	–	✓	✓
Hospitalisation	History of hospitalisation	✓	✓	–	✓	–	–	–	✓	✓
History of diagnosed disability	Diagnosed disability	✓	–	–	–	–	–	–	✓	–
Pubertal development	Menarche, voice-breaking and Tanner stages	✓	–	–	✓	–	✓	✓	✓	✓
Bullying	From previous school trials	✓	✓	–	✓	–	✓	✓	✓	✓
App feedback/acceptability										
App feedback	Future Proofing App Feedback Survey	–	✓	–	–	–	–	–	–	–
App feedback	Post-intervention SPARX-FP Feedback Survey	–	✓	–	–	–	–	–	–	–

*UNSW* University of New South Wales

^a^Participants selected to take part in Stage II of the trial only

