## Methods

### Trial design

This study is a randomised controlled, single-blind trial with two intervention stages, each consisting of two parallel arms (intervention and inactive control) with 1:1 allocation at each stage. Cluster randomisation will occur at the school level for the first intervention stage, stratified by school size, school location, school student gender and socio-economic status (full details in Randomisation section).

The second intervention stage will occur directly after the 12-month follow-up and involve individual-level randomisation. Stage I of the trial will have eight measurement occasions: baseline (pre-intervention); Stage I post intervention (immediately after completing the Stage I intervention, 6 weeks after baseline); and 6-month, 12-month (primary endpoint), 24-month, 36-month, 48-month and 60-month follow-up. The follow-up period is the time since baseline. For the subset of participants involved in Stage II of the trial, an additional measurement occasion will take place 6 weeks after the Stage II intervention (Stage II post intervention). The trial will take place in three recruitment waves. It was planned that Wave 1 will commence in Term 3, 2019 (July 2019), Wave 2 will commence in Term 2, 2020 (April 2020) and Wave 3 will commence in Term 3, 2020 (July 2020). The Stage I intervention phase (SPARX) will last 6 weeks and have a follow-up period of 5 years. The Stage II intervention phase (Sleep Ninja) will last 6 weeks, occurs 12 months after Stage I (SPARX) and will have a follow-up period of up to 4 years.

Data from each assessment point will be used to determine safety and whether any modifications to the trial protocol are required (see Analysis section for details). A concurrent implementation process evaluation will be conducted, and study processes may be modified to better address the needs of the school context. Any change will be reflected in the study protocol and registration (ACTRN12619000855123).

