### Additional outcome measures, potential mediators and risk factors

The following additional outcome measures will be examined and reported separately from the primary and secondary outcomes. Also included are variables which may mediate outcomes in the intervention arms. Potential risk factors for the development and maintenance of mental health disorders are also included (see Table 1 for the specific measurement occasions corresponding to each measure).

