### Linked data

Data relating to participants’ academic outcomes, physical health, utilisation of health services, infant development, births and deaths will be linked from extant Australian government administrative datasets by an authorised agency of the New South Wales Ministry of Health, the Centre for Health Record Linkage (CheReL, www.cherel.org.au). Informed consent from each participant will be obtained prior to linkage and databases will be linked using personal identifiers such as names, dates of births, addresses and hospital identification numbers with probabilistic methods. Linked data will be provided to the researchers in a de-identified manner and will be used to determine related health and other outcomes for the participant, including birth and perinatal data, educational outcomes in standardised curriculum-based tests, and hospitalisation and mortality outcomes. Linkage will occur within the first 12–24 months of the study (at the end of 2020) and will be updated periodically every 2 years until the trial concludes.

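### The hospitalisation item looks back 12 months but is skipped at 24 and 36 months, so no trial survey collects admissions from month 12 to month 36

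*Protocol article*

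**What the plan says.** - **Recall period.** The Hospitalisation section states: "One item will assess hospitalisation in the previous 12 months". The respondent separates physical from mental-health admissions. No other definition of the item is given.
- **Schedule.** Table 1, headed "Summary of primary, secondary and tertiary outcome measures, potential mediating and risk factors, and data collection time points", lists the item as "History of hospitalisation". Its nine cells match the nine column headings: ticks at baseline, Stage I post, 12, 48 and 60 months; dashes at 6 months, Stage II post, 24 and 36 months.
- **Which text sets the timing.** The section on additional outcome measures, mediators and risk factors defers to the table: "see Table 1 for the specific measurement occasions corresponding to each measure".
- **Time scale.** Under Trial design: "The follow-up period is the time since baseline".
- **Stage II.** Under Trial design: "The second intervention stage will occur directly after the 12-month follow-up and involve individual-level randomisation". The Hypotheses section includes a Stage II contrast from 12 to 24 months.
- **Second source.** The Linked data section plans administrative records that include hospital admissions, for participants who consent. A first linkage is expected at the end of 2020, and it "will be updated periodically every 2 years until the trial concludes".

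**The concern.** A question with a 12-month look-back gives continuous coverage only if it is asked at least once a year. This one is asked at 12 months and then not until 48 months. An admission in the second or third year falls outside every survey's recall period, and a later survey cannot retrieve it.

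The schedule looks unintended. The suicide-behaviour items, the bullying items and the romantic-relationship items also ask about the past year, and Table 1 ticks all three at every annual survey from 12 to 60 months. Hospitalisation instead has exactly the tick pattern of the lifetime mental-health diagnosis item. A lifetime question can skip two years and catch up later; a 12-month question cannot.

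At stake is the only survey item that records an admission, over a period that begins just as students with elevated depressive symptoms are randomised in Stage II.

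**Working it through.** The plan states no coverage figure to reproduce, so the check sets the recall period against the schedule.

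**Rule.** A survey at month *t* with a 12-month look-back covers the interval from *t* − 12 to *t*, where *t* is months since baseline (Trial design).

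| Survey with a tick | Interval covered (months) |
|---|---|
| Baseline (0) | −12 to 0 |
| Stage I post (about 1.5) | −10.5 to 1.5 |
| 12 | 0 to 12 |
| 48 | 36 to 48 |
| 60 | 48 to 60 |

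**Union over follow-up.** Months 0–12 and 36–60 are covered: 12 + 24 = 36 of 60 months. The uncovered period is months 12–36: 36 − 12 = 24 months, and 24/60 = 40%.

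**Overlap with Stage II.** The 12-to-24-month contrast lies wholly inside the gap (12 of 12 months). Counting a year from the end of the 6-week intervention instead (about months 13.5 to 25.5) gives the same answer.

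**Sensitivity to late completion.** The Procedure section allows 4 weeks to complete a survey, which is 28/30.4 ≈ 0.9 month. A student who is late at 12 months and on time at 48 has a gap of 36 − 12.9 = 23.1 months. One who is on time at 12 and late at 48 has a gap of 36.9 − 12 = 24.9 months. The edges move; the gap stays.

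**Timing of the linked source.** This assumes the planned start dates hold and refreshes fall at the end of 2020 and of 2022. Wave 2 starts in April 2020 and reaches month 12 in April 2021. Wave 3 starts in July 2020 and reaches month 12 in July 2021. The next refresh, at the end of 2022, is then about 20 and 17 months after Stage II opens for these waves. A 24-month survey would report 12 months after it opens.

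**With the item added at 24 and 36 months.** The new intervals are 12–24 and 24–36. The union becomes 0–60, with an uncovered period of 0 months at nominal dates. A student who is on time at one survey and late at the next could still have a gap of at most about 0.9 month.

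**The case against.** The strongest reply is that the trial does not depend on this item. The Aims and Linked data sections make administrative records a separate form of trial data and name hospital admissions among their outcomes. For students who consent to linkage, admissions in months 12 to 36 should therefore be available for comparison by arm. A reader might infer from the survey gap that such a comparison is impossible from trial data. The documents do not support that.

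A reader might also infer that the Data and Safety Monitoring Committee would be blind to harm in this period. That does not follow either. The risk management section says "The DSMC will be responsible for safeguarding the interests of participants through regular monitoring, including participant safety and adverse events", but nothing assigns the hospitalisation item to that committee or makes it the means of adverse-event capture. The Interim analyses section lists what the committee reviews: PHQ-A caseness, scores and suicidality. The PHQ-A, SIDAS, suicide-behaviour and self-harm measures are all ticked at 24 and 36 months. An annual question would in any case report a month-13 admission only at month 24, so it is not a real-time safety tool.

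The linking agency is in New South Wales and schools in other states may join, but the article refers to Australian government datasets and does not say that students elsewhere would go unlinked. No weight is placed on that point.

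The table label "History of hospitalisation" could suggest a lifetime question, which would remove the gap. The item's own section gives the 12-month period explicitly and is the only definition.

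These replies limit the consequence but do not remove the mismatch. Linkage requires its own consent, the proportion consenting is not given, and the refresh is every 2 years. Leaving the item out to reduce burden would be a defensible choice, but the article gives no such reason and keeps other 12-month items at the same visits.

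**Conclusion.** The point holds for survey-reported admissions. As written, 24 of 60 follow-up months (40%), including all of the 12-to-24-month Stage II period, are covered by no survey, and the 48-month answer cannot recover them. This rests on the 12-month recall in the Hospitalisation section and on the Table 1 row as printed.

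The practical loss has two parts. For students without linkage, admissions in that period are missing altogether; how many students this affects cannot be worked out from the article. For linked students, what is lost is an earlier second source.

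The importance is modest. Hospitalisation is an additional measure, months 0 to 12 are fully covered so the primary endpoint is untouched, and the stated Stage II hypotheses concern depression, anxiety and insomnia. It is worth correcting because the fix is cheap and the missed answers cannot be collected later with this item.

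**What to change.** In Table 1, tick the existing hospitalisation item at 24 and 36 months and keep its 12-month recall and its physical/mental split. The annual windows then cover months 0 to 60. Rename the table entry so that it no longer suggests a lifetime history.

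The cost is one extra question on each of two surveys that already take place. Table 1 ticks 25 measure rows at 24 months and 24 at 36 months, so the added burden is small. A minor amendment would be needed.

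Lengthening the look-back at 48 months to 36 months would also close the gap on paper. It would rely on much longer recall and would give no information until year four, so it is the weaker option.
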